##### Effects of SR on entomological endpoints

The frequencies and proportions of each mosquito genus and species (anopheline and non-anophelines) collected using HLC and light trap methods will be reported by cluster and treatment arm. The time profile plots of each of aggregated entomological endpoints will be obtained over the baseline and intervention phases. An appropriate statistical model for the HBR during the intervention phase will be identified after examining the distributional characteristics of the HBR data, which will likely follow (zero-inflated) Poisson distribution or (zero-inflated) negative binomial distribution if there is over-dispersion. The model will include treatment arm (SR vs placebo), relevant baseline covariates, and a random effect that accounts for the dependency among data collected from the same cluster. The ratio between SR and placebo in HBR will be estimated. A similar model will be applied to analyze the density of mosquitoes caught by light traps. The ratio between SR and placebo on light trap density will be estimated.

The model for parity rate will be based on the (zero-inflated) Poisson distribution or a (zero-inflated) negative binomial distribution with the daily parous mosquitos as the outcome and the daily HBR as the offset and the same set of covariates as those used in the model for analyzing HBR. The model for the sporozoite rate and EIR will be similar to the parity rate. If the data on parity, sporozoite positivity, and EIR are highly unbalanced (e.g., 99% nulliparous or 99% negative for sporozoites and EIR), then the model might lead to unstable estimates or the model might not even converge. In such cases, only summary statistics will be provided.

Summary statistics will be provided on insecticide resistance at baseline and each year during the intervention phase, aggregated over the clusters on SR.

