Existing malaria vector control guidelines do not recommend the use of SRs for personal protection [18]. However, various SR products have been shown to reduce mosquito biting [19–25] and, in epidemiological studies conducted in Indonesia [26], China [27], and Peru [28] have been shown to reduce pathogen transmission in human populations. In Indonesia, using a transfluthrin-based SR product, Shield with a 2-week duration of protection, a 27.7% reduction in time to first-event and 31.3% in overall infections was demonstrated, but outcomes were not statistically significant due to low incidence in some clusters at baseline, undermining the power to detect a protective effect [26]. Additionally, the study demonstrated a 16.4% and 11.3% reduction in anopheline attack rates indoors and outdoors of households (HHs), respectively. In the Peru trial, the same SR intervention was used, Shield, which significantly reduced arboviral infections by 34.1% with an associated reduction in *Aedes aegypti* abundance and blood-fed capture rates by 28.6% and 12.4%, respectively [28].

The Kenya trial described here will evaluate the efficacy of a next-generation formulation of the SR product used in the Indonesia and Peru trials, Mosquito Shield™, with a duration of protection up to 4 weeks. The choice to use the Mosquito Shield^TM^ product was based on this product containing the same active ingredient and design (i.e., passive emanator) as was used in clinical trials dating back to 2013 which demonstrated impact to reduce malaria and arbovirus infections [28, 29]. Thus, preliminary public health value data exists for this “first-in-kind” prototype for the SR class. The study also been designed to demonstrate whether deployment of SRs will or will not result in increased malaria transmission and disease among geographically proximal non-users.

This evaluation will serve as a proof-of-principle of SR product protective effect for sub-Saharan Africa. Trial results will be submitted to the WHO Vector Control Advisory Group (VCAG) to contribute to the body of evidence regarding the impact of SRs in reducing human malaria infections in settings where underlying transmission rates are high at baseline, ITNs are widely deployed, and/or where mosquito vectors bite outdoors. The outcomes of this study will inform policy recommendations for SRs as a means to further reduce malaria transmission.

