### Outcomes {12}

The primary outcome measure of this cRCT will be the first-time malaria incidence rate as measured by microscopy in children aged ≥ 6 months to 10 years.

Secondary outcome measures include:
Overall new *Plasmodium falciparum* malaria infections, as measured by microscopy;The first-time and overall *P. falciparum* malaria infections in buffer zones, as measured by microscopy;The first-time and overall *P. falciparum* malaria infections by two age groups (≤ 59 months old; 5 years old to 9 years and 11 months old), as measured by microscopy;Anopheline-human contact (indoor and outdoor) using human biting rate (HBR) as an indicator for all anophelines and by anopheline species, as measured by HLC during 12-h intervals on a quarterly basis;Anopheline survival and population age structure using parity rate as an indicator for all anopheline and by anopheline species, as measured by mosquito ovarian dissections from a sub-sample of anophelines collected during HLC procedures;Anopheline infectivity using sporozoite rate as an indicator for all anopheline and by anopheline species, as measured by laboratory detection of sporozoites in mosquito heads and thoraces from a sub-sample of anophelines collected during HLC and/or CDC light trap collections;Entomological inoculation rate (EIR) as an indicator of transmission intensity for all anophelines and by anopheline species, as measured by calculating the number of sporozoite-infected anopheline mosquitoes captured per person from CDC light trap and/or HLC collections;CDC light trap indoor density for all anophelines and by anopheline species, as measured by light trap collections during 12-h intervals on a monthly basis;Insecticide resistance, as measured by WHO filter paper test and CDC bottle assays during baseline and intervention phase.Adverse events (AEs) and serious adverse events (SAEs), as measured by solicited and unsolicited reports during baseline and intervention phase. Mean, minimum, and maximum frequency and percentage of AEs and SAEs across clusters among enrolled subjects will be summarized by treatment arm.

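### With the human biting rate as the only stated offset, the EIR model estimates the sporozoite-rate ratio instead of the per-person EIR ratio, and parity and sporozoite rate get the wrong denominator

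*Protocol article*

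**What the plan says.** Under *Effects of SR on entomological endpoints*, parity gets a Poisson or negative binomial model, possibly zero-inflated, "with the daily parous mosquitos as the outcome and the daily HBR as the offset". For the next two endpoints the section says only: "The model for the sporozoite rate and EIR will be similar to the parity rate". Biting has its own model: "The ratio between SR and placebo in HBR will be estimated".

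Outcomes {12} sets the quantities these models should estimate:

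- EIR is obtained "as measured by calculating the number of sporozoite-infected anopheline mosquitoes captured per person from CDC light trap and/or HLC collections".
- Parity is taken "as measured by mosquito ovarian dissections from a sub-sample of anophelines collected during HLC procedures".
- The sporozoite rate is taken "from a sub-sample of anophelines collected during HLC and/or CDC light trap collections".

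EIR therefore has a person denominator, and the other two are proportions of the mosquitoes actually processed.

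**The concern.** A repellent is expected to act mainly by reducing contact between people and vectors. EIR combines that contact with mosquito infection, so it should move when biting falls. An HBR offset conditions on biting and removes that pathway from the endpoint. Sporozoite rate and EIR also share a numerator, the sporozoite-positive mosquitoes. With one offset for both, two endpoints that Outcomes {12} lists separately become a single estimate under two names.

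There are two practical signs of the mismatch. A night with zero HBR has no defined log offset, although it is a valid zero for EIR. And light-trap catches, which Outcomes {12} allows for both sporozoite rate and EIR, yield no HBR.

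Parity and sporozoite status come from sub-samples. HBR counts the whole catch, so it is not the denominator of either proportion.

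**Working it through.** The article gives no effect size or power figure for these endpoints, so there is no stated figure to reproduce.

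**1. EIR, algebra.** Let h be the HBR in an arm (mosquitoes per person-night) and s the sporozoite rate, with all mosquitoes tested. Expected infected mosquitoes per person-night are h × s, which is the EIR as defined. With a log link and offset log(h):

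log E[infected] = log(h) + a + b × arm, so exp(b) = ratio of (h × s)/h = ratio of s.

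Equivalently, b = log(EIR ratio) − log(HBR ratio).

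**2. EIR, numbers.** The article's own anopheline biting figures are "a 16.4% and 11.3% reduction in anopheline attack rates indoors and outdoors of households" in the Indonesian trial (Background and rationale {6a}). These give HBR ratios of 1 − 0.164 = 0.836 and 1 − 0.113 = 0.887. The sporozoite-rate ratios below are an assumed range.

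| Sporozoite-rate ratio | EIR ratio, indoors (× 0.836) | EIR ratio, outdoors (× 0.887) | HBR-offset model |
|---|---|---|---|
| 1.0 | 0.836 | 0.887 | 1.0 |
| 0.9 | 0.752 | 0.798 | 0.9 |
| 0.8 | 0.669 | 0.710 | 0.8 |

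**3. EIR, simulation.** The layout follows Trial design {8}: 6 clusters × 4 houses × 2 nights × 8 quarters = 384 house-nights per arm. Assumed values are a mean catch of 20 per night, sporozoite rate 5%, parity 60%, between-cluster SD 0.3 on the log scale and over-dispersed catches. A Poisson GLM was fitted in 300 replicates. With a true HBR ratio of 0.836 and all mosquitoes tested:

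- Sporozoite-rate ratio 1.0: 0.998 with HBR offset, 0.843 per person-night.
- Sporozoite-rate ratio 0.8: 0.801 with HBR offset, 0.677 per person-night.

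The small gaps from 0.836 and 0.669 are simulation error. The cluster term alone gives a standard error of 0.3 × √(2/6)/√300 = 0.010 on the log scale.

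**4. Parity and sporozoite rate.** Let f be the fraction of the catch processed and p the true proportion positive. The expected positive count is h × f × p. Dividing by h leaves f × p, so:

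- the absolute rate is too low by the factor f;
- the arm ratio is the true ratio × (f in SR)/(f in placebo), which is unbiased when f is equal in the two arms.

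The simulation agrees. With a constant 30% sub-sample and a true sporozoite-rate ratio of 0.8, the HBR offset gives 0.797. A nightly cap on the number processed is different, because f then rises as catches fall. With no true effect on parity or sporozoite rate:

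| HBR ratio | Cap per night | Parity ratio, HBR offset | Sporozoite ratio, HBR offset | Parity ratio, dissected as offset |
|---|---|---|---|---|
| 0.836 | 10 | 1.154 | 1.146 | 1.001 |
| 0.836 | 5 | 1.186 | 1.188 | 0.999 |
| 0.70 (assumed) | 5 | 1.377 | 1.374 | 0.999 |

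The caps are assumptions; the article states no sub-sampling rule.

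**5. Sub-sampling also affects a corrected EIR model.** Under a cap of 10, the infected count per person-night, left unscaled, gives 0.952, although the biting ratio in those runs was 0.830 and the sporozoite rate was unchanged. A person-night offset alone is therefore not enough if the fraction tested varies.

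**The case against.** The strongest reply is that the HBR offset is written only for parity, and that *similar* is used loosely in this article. Light-trap density also gets a similar model with a different outcome, and the overall-infection and diversion analyses get similar models with added terms. Since light traps yield no HBR, the offset could not be carried over literally there. The authors may have meant only the same model family and covariates. This stands in part: a reader might infer that the trial will certainly report a sporozoite-rate ratio as its EIR effect, and the text does not go that far. But HBR is the only offset named. The same section's fallback for sparse data also describes EIR as if it were a share of mosquitoes testing negative, which favours the per-mosquito reading.

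Four other stronger readings are tempting and not supported:

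- *The biting effect would vanish from the report.* It would not. The HBR and light-trap density ratios are estimated separately, and the HBR ratio × the sporozoite-rate ratio recovers the EIR ratio. However, nothing in the article tells the reader to do this.
- *The parity and sporozoite ratios are biased.* That requires processed fractions that differ by arm. The article does not suggest this, and staff are blinded. A catch-dependent rule such as a cap could produce it despite blinding, but the article neither states nor excludes one.
- *Zero-catch nights are lost from all three analyses.* For parity and sporozoite rate such nights carry no information. The loss matters only for EIR.
- *The benchmark objective fails.* The examples in Objectives {7} do not name EIR, and the analysis linking entomology to malaria hazard uses HBR and light-trap density.

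The EIR model may also never be fitted, because the plan falls back to summary statistics when nearly all results are negative.

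**Conclusion.** The point holds as an inconsistency between the definition of EIR and the only model offered for it. Followed as written, the EIR arm effect is the sporozoite-rate ratio: about 1.00 where the per-person ratio is about 0.84 indoors (or 0.89 outdoors), given the Indonesian biting reductions and an unchanged sporozoite rate. The cancellation is algebraic and does not depend on the simulated catch or infection rates. Exact equality with the sporozoite-rate ratio assumes that all mosquitoes, or the same fraction in each arm, are tested.

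For parity and sporozoite rate, HBR is the wrong denominator. Absolute rates are mis-scaled by the fraction processed; bias in the SR/placebo ratio is conditional on that fraction differing by arm.

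The reach is limited to secondary entomological endpoints. The primary hypothesis and the malaria analyses are untouched.

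**What to change.** State the denominator for each endpoint under *Effects of SR on entomological endpoints*:

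- **EIR:** infected count with offset log(person-nights) for landing catches or log(trap-nights) for light traps, no HBR term, zero-catch nights kept. If only part of the catch is tested, scale the infected count by caught/tested. Alternatively, report HBR ratio × sporozoite-rate ratio with an interval that respects clusters, such as a cluster bootstrap.
- **Parity:** number dissected as the denominator.
- **Sporozoite rate:** number tested as the denominator.

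For the last two, a count model with that offset or a binomial mixed model is acceptable. Stating the sub-sampling rule as well would let a reader see whether the processed fraction can depend on the catch.

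The cost is wording and model code, since the numbers dissected and tested arise from the assays anyway. The change should be made before the unblinded analysis, because changing an offset after seeing results by arm would look selective.

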Twenty clusters (10 SR, 10 placebo) will be randomly selected to estimate the impact of the SR on entomological measures of malaria transmission. These clusters will remain fixed throughout the study. Within each of the 20 clusters, light trap collections will be conducted monthly in 10 randomly selected HHs within the core area of each sentinel cluster to assess the impact of SRs on the density of *Anopheles* mosquitoes indoors. On the same night, light trap collections will also be conducted in 15 randomly selected HHs in the buffer zone of the same cluster to estimate the diversionary effect of the SR. Human landing catches (HLC) will be performed indoors and outdoors of 48 HHs in a subset of 12 (6 SR intervention, 6 placebo) of the 20 clusters selected for entomology evaluation to determine the effect of SR on the host seeking behavior of mosquitoes. The 12 clusters will remain fixed throughout the study. Sampling will be performed in four houses (randomly selected) in each cluster for two nights once every quarter (3 months). The same houses will be sampled each quarter.

Each cluster will consist of a core area, which corresponds to an existing village, and a buffer zone which includes HHs outside but within 300–500 m of the core area (Fig. 1). Based on studies evaluating mass effect of ITNs [30], endpoints measured in the buffer zone in our trial will be used to quantify induced diversion by the SR intervention on mosquitoes from within cluster core areas to locally unprotected individuals in the buffer zones thereby potentially having a differential impact on malaria infection incidence among protected and locally unprotected individuals.

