## Interventions

### Explanation for the choice of comparators {6b}

According to the WHO VCAG’s guidelines for vector control field trial design, studies should always have a control group from which data collection occurs contemporaneously with data collection from the intervention group [34]. Our trial design includes a placebo product of matched design to the Mosquito Shield™ but with inert ingredients only. The use of a placebo is generally acceptable when a placebo is compared against an intervention in combination with standard treatment [35]. Our study design will not withhold standard-of-care for clinical management of malaria nor standard-of-care vector control interventions (e.g., LLINs, indoor residual spraying (IRS)) in either the SR or placebo arm, but instead, these will be monitored and recorded throughout the trial. This approach is aligned with WHO VCAG guidance that the control group must receive care reflecting the standard best practice interventions like routine vector control measures, such as LLINs distributed through mass campaigns, and routine health systems such as antenatal clinics or Expanded Programme on Immunization (EPI) visits. Study participants will also be encouraged to continue use of LLINs and not instructed to avoid alternative vector control tools (e.g., coils, topicals, aerosol sprays, repellents).

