### Relevant concomitant care permitted or prohibited during the trial {11d}

Our study design will not withhold standard-of-care for clinical management of malaria nor standard-of-care vector control interventions (e.g., LLINs, IRS) in either the SR or placebo arm, but instead, these will be monitored and recorded throughout the trial. All children enrolled in the cohort will be provided a new LLIN. Study participants will be encouraged to continue use of LLINs and not instructed to avoid alternative vector control tools (e.g., coils, topicals, aerosol sprays, repellents). This will allow us to estimate the effect of the SR assuming all other measures are still occurring for malaria prevention, essentially providing insight on an additive benefit above that provided by currently recommended WHO malaria preventive measures. At baseline, children enrolled into the cohorts will be provided a treatment dose of AL free of charge according to Kenya national treatment guidelines to clear any prepatent or patent malaria parasites. Lastly, subjects will be provided treatment for malaria infection throughout the follow-up period.

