## Assignment of interventions: Allocation

### Sequence generation {16a}

For the baseline cohort, recruitment of participants for enrolment was based on random selection of HHs using census mapping of the study area. Random allocation of clusters into treatment assignment will be performed during baseline following interim analysis of incidence and prior to cohort 1 participant enrolment. Baseline estimates of incidence will be used to guide decisions on cluster stratification. A total of 60 clusters (30 per treatment arm) will be randomly allocated to receive either the SR intervention or placebo treatment. The cluster allocation sequence will be generated by the external statistician serving on the Data Safety Monitoring Board (DSMB) using a random number generator (https://www.random.org).

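### Insecticide resistance, a secondary outcome, is to be summarised in SR clusters only, so the planned series cannot separate a background trend from any effect of the product (minor)

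*Protocol article*

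**What the plan says.** Under Outcomes {12}, the article includes this among the secondary outcome measures: "Insecticide resistance, as measured by WHO filter paper test and CDC bottle assays during baseline and intervention phase". Nothing there confines the measurement to one arm.

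Under Effects of SR on entomological endpoints, the analysis is fixed as: "Summary statistics will be provided on insecticide resistance at baseline and each year during the intervention phase, aggregated over the clusters on SR". This is all the article says on how resistance will be analysed.

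The same section treats the other entomological data differently. Mosquito genus and species counts "collected using HLC and light trap methods will be reported by cluster and treatment arm". The human biting rate model has a treatment term and yields an SR-to-placebo ratio. For light traps, "The ratio between SR and placebo on light trap density will be estimated". The parity model reuses the biting-rate covariates, and the sporozoite rate and EIR models are described as similar.

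**The concern.** A listed secondary outcome of a randomised trial, analysed under a heading about effects of SR, is reduced to a before-after series in the treated arm. Resistance in local mosquitoes can change over two years for reasons unrelated to the product, and a one-arm series has no means of showing that.

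What is at stake is whether this one outcome can be interpreted. A change in SR clusters could be background, product or a mixture, and stability could hide two opposing influences. The sentence states a choice that leaves the placebo arm out of the summary, so it is more than a detail that the article leaves to a fuller document.

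**Working it through.** The article gives no assay counts, baseline resistance level or expected trend, so there is no planned figure to reproduce. The check sets the relevant places side by side and asks what the planned summary estimates.

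**Inputs from the protocol article**

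- Outcome: resistance, measured at baseline and during intervention, no arm limit (Outcomes {12}).
- Planned summary: SR clusters only (Effects of SR on entomological endpoints).
- Randomised control: "A total of 60 clusters (30 per treatment arm) will be randomly allocated to receive either the SR intervention or placebo treatment" (Sequence generation {16a}).
- Entomology clusters: "Twenty clusters (10 SR, 10 placebo) will be randomly selected to estimate the impact of the SR on entomological measures of malaria transmission" (Trial design {8}).
- Stated principle, citing WHO VCAG guidance: "studies should always have a control group from which data collection occurs contemporaneously with data collection from the intervention group" (Explanation for the choice of comparators {6b}).
- Background exposure in both arms: "All children enrolled in the cohort will be provided a new LLIN"; standard vector control is not withheld in either arm, and participants are not told to avoid other mosquito-control products (Relevant concomitant care {11d}).

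**What each summary estimates**

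Let T be the background change in resistance from baseline to a given intervention year, E the effect of the product in SR clusters, and S any part of that effect that reaches placebo clusters through mosquito movement.

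- Expected change in SR clusters = T + E.
- Expected change in placebo clusters = T + S.
- SR change minus placebo change = (T + E) − (T + S) = E − S.

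The planned summary gives only T + E. For any observed change x, every pair with T = x − E fits equally well.

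**Illustration (assumed figures, not from the article).** Suppose the SR series moves by 10 percentage points, and take S = 0.

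| Background T | Product effect E | SR change T + E | Placebo change T | Difference |
|---|---|---|---|---|
| 10 | 0 | 10 | 10 | 0 |
| 0 | 10 | 10 | 0 | 10 |
| 15 | −5 | 10 | 15 | −5 |

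The SR column is the same in all three rows. Only the placebo column tells no effect, an effect in the direction of the trend and an effect against it apart. If S is not zero but smaller than E and of the same sign, the difference shrinks towards zero and keeps its sign.

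**Is T plausibly non-zero?** The article gives no trend. It does describe continuing insecticide exposure in both arms (new nets for cohort children, other vector control continuing), so it offers no ground for assuming T = 0.

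**The case against.** The strongest reply is that the article never undertakes to estimate an effect of SR on resistance. The entomological objective concerns correlates of transmission, and resistance is not among its examples. The formal hypotheses concern first-time and overall malaria only. Resistance gets summary statistics with no model, ratio or test, which fits descriptive monitoring of the vector population exposed to the product. No decision or stopping rule depends on it.

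Most of this stands, and it rules out several stronger readings:

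- A reader might infer that the trial sets out to test whether the repellent selects for resistance and fails to do so. No section states that aim. The Discussion's remark that SRs may lessen selection pressure is hedged background, not a claim the trial promises to examine.
- A reader might infer that a rise in resistance would be reported as caused by the product. Nothing in the article says so.
- A reader might infer that placebo data are collected and then thrown away. The article does not say which clusters supply mosquitoes for the assays or how many assays are run, and its light-trap and landing-catch sampling plans do not mention resistance testing.

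The remedy also has limits. Buffer zones reach 300–500 m into neighbouring villages and the trial itself considers diversion of mosquitoes, so S may not be zero. With 10 entomology clusters per arm, a contrast would be imprecise if the assays use those clusters.

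What does not stand is the step from descriptive to one-arm. A summary by arm is equally descriptive, needs no hypothesis or power claim, and can be interpreted. Dilution and imprecision limit what a contrast can show, but they do not make a series without a control more informative.

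**Conclusion.** The point holds as a minor one. As written, the resistance outcome would be uninformative about SR, because the planned series estimates background change plus product effect and cannot split them. It is the only endpoint in its section expressly confined to one arm, and it departs from the principle of contemporaneous control data that the article cites.

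The practical size is unknown. The error in reading the SR series as a product effect would equal the whole background change T, for which the article gives no value. The conclusion rests on two assumptions: that T may differ from zero, and that the sentence means what it says in limiting the summary to SR clusters. The tests of first-time and overall malaria infection, their type I error and their power are untouched.

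**What to change.** In Effects of SR on entomological endpoints, replace the restriction to SR clusters with descriptive summaries of resistance by treatment arm at baseline and in each intervention year, together with the between-arm difference in change from baseline, wherever placebo clusters are assayed. State which clusters supply the assays, and note that mosquito movement and the small number of entomology clusters may dilute the contrast. No hypothesis test is needed.

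Where placebo clusters are already assayed, the cost is a few more table columns. If assays cover SR clusters only, say that the series is monitoring and supports no statement about an effect of SR on resistance; this costs one sentence. Dividing a fixed number of assays between the arms is a possible alternative, but a real trade-off: it leaves fewer assays in the exposed population, widens the interval for each arm, and may require new collections in placebo clusters.
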